### Study design and summary

This was a cohort study with the following characteristics: population based, prospective, longitudinal, and performed in three stages (Fig. 1). In the first stage, clinical, nutritional, and anthropometric evaluations, measurements of serum and urinary markers for CKD, and examinations for comorbidities (systemic arterial hypertension [SAH], DM, CVD, obesity, and dyslipidemia) were performed. The second stage consisted of repeated examination of individuals with CKD, SAH, and/or DM, image screening, and cardiac risk assessment. The third stage included long-term monitoring of all selected individuals.

**Fig. 1 Fig1:**
[figure not shown]
Flowchart of PREVRENAL study stages

### Research team and study timeline

The PREVRENAL team is coordinated by two nephrologist researchers and is composed of: two nephrologists, three cardiologists, two imaging experts (one radiologist and one vascular surgeon), two epidemiologists, four nurses, five nutritionists, two social workers, four biochemists, nine graduation students, and three drivers equipped with four-wheel-drive vehicles. Trips for the first stage’s active search were performed on non-holidayweekends, during a nine-month period from August 2012 to April 2013. Image experts did not participate during this stage. All researchers were trained on the project’s basic procedures.

### First stage

#### Data collection

A questionnaire was completed for each adult in each household. Individual questionnaires were divided into blocks with the following subjects: basic demographic information (age, gender, marital status, and migration); socioeconomic characteristics (education, occupation, working relationship, and income); personal habits (smoking, alcoholism, diet type, and physical exercises); clinical data; arterial blood pressure(AP) status; previous disease of the cardiovascular, renal, and respiratory systems; medications; and health services usage. A minor diet survey was conducted in each family (including sodium content) by nutritionists.

#### Anthropometric measurements and arterial blood pressure

Weight was measured using an electronic scale with 150 kg maximum capacity, and height was measured using a portable anthropometer with 0.1 cm accuracy. Measurements were performed by two independent researchers. Individuals were barefooted, wearing light clothes, and in the orthostatic position. Body mass index(BMI) was calculated and classified according to the International Obesity Task Force (IOTF) criteria. Waist circumference and reference values for gender, age, and ethnicity were defined per NHANES III. AP measurement was performed on the right arm of seated individuals using a proper cuff, which covered 80% of the distance between the olecranon and acromion. The pneumatic bag covered at least 40% of the arm circumference at the level of the heart. Three measurements were performed with a three-minute interval between them and after a five-minute rest; then, the average of the last two measurements was used. The oscillometric method was used for AP assessment using a certified device.

#### Blood and urine collection

Blood was collected after a 12-h fast and the following tests were performed: serum creatinine, urea, cystatin C, glucose, calcium, phosphorus, albumin, cholesterol (total, HDL, and LDL), triglycerides, serum iron, transferrin, glutamic-pyruvic transaminase, ultrasensitive C-reactive protein, and hemoglobin. Total blood and serum samples were collected for freezer storage at − 80 °C. A genetic/ethnic study and evaluations of inflammatory markers (IL-6, TNFα) and APOL 1 polymorphism will be performed using these samples.

Urine sample was collected by the individuals at home and used for testing creatinine, albumin, abnormal elements, and sediment. A second urine collection was used for testing sodium excretion. Estimates for creatinine excretion within 24 h (PrCr24h) and causal urine sodium/creatinine ratio (NaUr) were obtained for estimating the 24-h sodium excretion (Na24h) of isolated samples, per Kawasaki’s Equation [14] (Kawasaki, 1993), which was certified for the Brazilian population.

#### CKD diagnosis

CKD diagnosis was considered for those individuals presenting with a GFR ≤60 mL/min/1.73m^2^ and/or albuminuria > 30 mg/day. The first parameter relates to functional damageand the second indicates structural lesions of the filtration barrier [15, 16] (KDIGO, 2013; LEVEY; BECKER; INKER, 2015). For CKD diagnosis confirmation, GFR and albuminuria tests were repeated three months after the first test. GFR was estimated using four equations, of which three are from the Chronic Kidney Disease - Epidemiologic Collaboration Equation (CKD-EPI) study as follows: 1) one equation based on creatinine values [17]; 2) one equation based on cystatin C values; and 3) one equation based on both creatinine and cystatin values [18]. Serum creatinine was measured using the modified Jaffé’s method. Immunoturbidimetry was used to measurecystatin C.

### Second stage

#### Cardiovascular risk

Cardiovascular risk assessment was performed using Framingham’s risk score [19]. Arteriosclerosis was also evaluated using two-dimensional ultrasonography of the carotid arteries and computerized tomography of the coronary arteries, in addition to tomographic measurement of visceral fat.

##### Carotid artery two-dimensional ultrasonography

Carotid intima-media thickness (CAIMT) was measured using an ultrasonography device (Vivid3, Vingmed GE, Horten, Norway). Examination was performed by a single experienced blinded examiner, who was not aware of the patient’s clinical and laboratory information, and risk classification. Bilateral carotid system evaluation was performed after at least 10 min of rest in the supine position with the neck in slight hyperextension. CAIMTwas measured at the artery wall of the common carotid, most distal to the transducer and 1 cm from the artery bifurcation. Measurements consisted of the distance between two echogenic lines traced at the lumen-intima and media-adventitia interfaces, and were considered normal when CAIMT< 0.9 mm, and abnormal when CAIMT > 0.9 mm [20].

##### Abdominal computerized tomography (CT)

Multi-slice helical CT was performed using a 64-channel CT scanner (Aquilion, Toshiba, Tokyo, Japan). First, a 10 mm unique volumetric section is axially performed under apnea (equivalent to 34 × 0.29-mm thick submillimeter cuts). A tomographic section of the lumbar region at the navel level, corresponding to the L3-L4 height, is usually topographically equivalent to the renal hilum projection (variation is defined depending on each patient’s renal hilum height). Examination was performed with a 0.4–0.6 s exposure time, field of view corresponding to the sample’s frame size (between 320 and 440 m), and 120 kV energy potential at 340 mAs.

Visceral fat analysis was performed at the workstation, using appropriate and specific software for the CT scanner, capable of differentiating all abdominal structures contained in the obtained volumetric section. Subsequently, each section’s tridimensional reconstruction was obtained, where all structures and organs are displayed through a color scale that is subjectively standardized by the researcher, facilitating tissue visualization, e.g. visceral fat. After the reading and design stages, quantitative abdominal visceral fat calculation is automatically performed by the software and expressed as volume per mL. Section points were defined as ≤102.5 cm^3^ (mL) for men and ≤84.1 cm^3^ (mL) for women [21].

##### Computerized tomographyof coronary arteries

Images were obtained using the same equipment. Each patient was placed in the supine position, and 3.0-mm thick (on average) images were obtained without intervals. Calcium presence was measured when the density was above 130 Hounsfield units in at least three continuous pixels (>1mm^2^) of the same artery. The coronary calcium score was composed of the sum of individual scores from the left and right coronary arteries and was analyzed and divided into categories according to the methods ofMcCellandet al [22].

##### Cardiac and renal echo-Doppler

All individuals with reduced GFR, SAH, DM, and/or high albuminuria were referred for echo-Doppler evaluation (Vivid3, Vingmed GE, Horten, Norway), with second harmonic and sectorial electronic transducer at 2–4 MHz. Cardiac and renal evaluations were performed. Cardiac evaluation consisted of thoracic echo-Doppler cardiogram, in which the following parameters were analyzed: ventricular geometry, systolic function, and diastolic function, according to the American Society of Echocardiography (ASE) recommendations [23, 24]. Renal evaluations consisted of obtaining the intrarenal resistive index, using renal Doppler, according to the methods ofRadermacher [25] (2002). In summary, analysis was performed using pulsed wave Doppler, obtaining the peak systolic (Vmax) and diastolic (Vmin) velocities; the index was calculated using the following equation: 100 x [1 - (Vmin/Vmax)]. The intrarenal resistive index (IRI) was calculated as the average of measurements performed for the upper, medium, and lower segments of both kidneys.

#### Chronic kidney disease (CKD) confirmation

All individuals with reduced GFR, SAH, DM, and/or high albuminuria were re-examined after three months in order to confirm the diagnosis of CKD.

### Third stage

All individuals selected for the first stage will be re-visited and all examinations will be repeated five years after the first stage.

### Statistic analysis

First, a descriptive analysis of the variables under study will be performed. Quantitative variables will be presented by mean and standard deviation and qualitative variables by frequencies and percentages. The Shapiro Wilk test will be used to evaluate the normality of the quantitative variables.

For categorical variables, group comparison will be based upon the results of the Chi-square test. Chi-square test will be replaced by Fisher’s exact test if the expected frequency in any of the cells of the contingency table is less than 5. For continuous variables, group comparison will be based upon the results of the *t*-test or the Wilcoxon rank-sum test, depending on the normality.

In the primary analysis, the prevalence of CKD at baseline and its corresponding 95% confidence interval (CI) will be presented. Prevalence of hypertension, diabetes mellitus, cardiovascular disease and other comorbidities at baseline and their corresponding 95% CIs will also be presented.

In the secondary analysis, the factors associated with the presence of CKD through bivariate analysis with an unadjusted prevalence ratio estimate and a 95% confidence interval (95% CI) will be used. The independent variables that present a significance lower than 0.20 (*p*-value < 0.20) will be considered in the final model, that is, in the adjustment of potentially confounding variables through the multivariate logistic regression technique performed step by step.

The comparison of survival (based on all-cause mortality) between patients with and without CKD will also be performed based upon the log-rank test performed at a significance level of 0.05. Hazard ratios and 95% CIs will be calculated by a Cox proportional hazard regression model.

The data will be analyzed in the statistical program STATA 12.0.

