## Methods and study design

### Study location and population

This study was performed in Alcântara, Brazil, a city located on the west coast of the State of Maranhão (Northeastern Brazilian region). This city has 21,851 inhabitants, with 15,452 individuals (70.71%) from rural populations distributed among 139 isolated African-descent communities (quilombos). Ancestors of the evaluated ethnic group were from the Ivory Coast, Angola, and Mozambique. Criteria used for ethnicity definition was the same as that used by the Brazilian Geography and Statistics Institute, which adopts self-assignment, posteriorly confirmed by genetic examination.

The sample individuals of this study were selected through probability sampling, which was designed in three stages. First, there was a randomized selection of census sectors, with probabilities proportional to population sizes. Second, households were randomly selected. Third, individuals aged over 18 years old, who lived in the selected households, were included in the study sample. Total sample size was estimated per 15% CKD prevalence expectation, with 2% sampling error, and 95% confidence level, composing a minimal sample of 1224 individuals. Finally, 1539 individuals were selected from 32 quilombo communities. The following were excluded from the sample: individuals under 18 years old, pregnant women, and patients with chronic consumptive disease, hematological diseases, autoimmune diseases, infections, chronic or acute kidney diseases undergoing dialysis treatment, thyroid disease, and those using immunosuppressant drugs, based on clinical history and physical examination.

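### The sample is drawn in clusters (census sectors, then households), but the sample size and the named tests treat people as independent, and nothing in the article allows for clustering

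*Protocol article*

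**What the plan says.** The section on study location and population of the protocol article describes three sampling stages. At the first, "there was a randomized selection of census sectors, with probabilities proportional to population sizes". At the second, "Second, households were randomly selected". At the third, "individuals aged over 18 years old, who lived in the selected households, were included in the study sample". The data collection section confirms that household members enter together: "A questionnaire was completed for each adult in each household". The result is 1539 people from 32 of the 139 communities. The minimum sample of 1224 is based on an expected prevalence of 15%, a sampling error of 2% and 95% confidence.

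The section headed Statistic analysis gives the primary analysis as "the prevalence of CKD at baseline and its corresponding 95% confidence interval (CI) will be presented". For categorical variables, "group comparison will be based upon the results of the Chi-square test", with Fisher's exact test for sparse tables. Continuous variables get a t-test or Wilcoxon rank-sum test. Associations use unadjusted prevalence ratios and stepwise logistic regression, and mortality uses the log-rank test and Cox regression. STATA 12.0 is the program. Clusters, weights, a design effect, survey estimation and robust variance are not mentioned.

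**The concern.** People in the same sector or household may be more alike in CKD status than people drawn at random from the whole population. Where that is so, 1539 people carry less information than 1539 independent draws, and formulas that assume independence understate the standard error. Selection proportional to size may make the sample nearly self-weighting, but it does not remove this loss.

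Two results are exposed. The first is the prevalence of CKD with its interval, which is the main product of the study and is meant to inform public policy. The second is the set of association analyses, above all for factors shared within a community or household. Diet, for example, is surveyed per family. P-values that are too small would also let such factors through the 0.20 screen into the final model more often than intended.

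**Working it through.** **Inputs from the article.** Prevalence p = 0.15; margin d = 0.02; z = 1.96; stated minimum 1224; 1539 people in 32 of 139 communities.

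**Inputs assumed.** The ICC is not given, so a range of 0.005 to 0.05 is shown. The number of census sectors is not given either, so the 32 communities stand in for them: m = 1539/32 = 48.1 people per cluster.

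**Step 1: reproduce the plan's figure.** n = z²p(1−p)/d² = 1.96² × 0.15 × 0.85 / 0.02² = 1224.5. This matches 1224 with a design effect of exactly 1. A finite-population correction would have given about 1135 (population 15,452) or 1160 (population 21,851), so neither was used.

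**Step 2: effect on the interval at n = 1539.** The interval that ignores clustering has half-width 1.96 × √(0.15 × 0.85/1539) = 1.78 points. With clustering:

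- design effect (DEFF) = 1 + (m − 1) × ICC
- required half-width = 1.78 × √DEFF
- actual coverage of the unadjusted interval = 2Φ(1.96/√DEFF) − 1
- with a finite-population correction, DEFF is multiplied by 1 − 32/139 = 0.77. Applying this to the whole variance is generous to the plan.

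| Assumed ICC | DEFF | Half-width needed (points) | Coverage, unadjusted | Coverage, with correction |
|---|---|---|---|---|
| 0.005 | 1.24 | 1.98 | 92.2% | 95.6% |
| 0.01 | 1.47 | 2.16 | 89.4% | 93.5% |
| 0.02 | 1.94 | 2.49 | 84.0% | 89.1% |
| 0.05 | 3.35 | 3.27 | 71.5% | 77.7% |

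**Step 3: what the surplus buys.** 1539/1224.5 = 1.257. Without the finite-population correction, the planned 2 points therefore hold up to DEFF 1.257, that is, an ICC of 0.257/47.1 = about 0.0055.

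**Step 4: households alone.** The article does not give the number of adults per household. With 2 to 3 adults and a within-household correlation of 0.05 to 0.20 (both assumed), DEFF runs from 1.05 to 1.40 and unadjusted coverage from 94.4% to 90.2%.

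**Step 5: tests.** For a factor that is constant within a community, a nominal 5% test rejects a true null hypothesis with probability 1 minus the unadjusted coverage: about 7.8%, 10.6%, 16.0% and 28.5% at the four ICCs. For factors that vary mainly within communities, such as age or sex, the inflation is smaller.

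**The case against.** The strongest reply is that the article never says how the primary interval will be computed. It is a condensed report, an analysis plan that is not shown may specify survey estimation, and the sample-size formula shows how the study was sized, not how it will be analysed. This stands as a limit: the unadjusted primary interval is inferred. It does not dispose of the point. The statistics section goes down to the switch from chi-square to Fisher and the screening threshold, and the tests it names do not fit the sampling it describes.

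A second reply is that an ICC needs differences between communities, while the Discussion describes ancestry, diet and low socioeconomic status as common to the whole population. This also stands and makes a small ICC plausible. With the finite-population correction, DEFF stays at or below 1 up to an ICC of about 0.0064 (1/0.77 = 1.299; 0.299/47.1). That credit applies only if inference is confined to these 139 communities. Homogeneity across communities also does not rule out correlation among relatives in one household.

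Some stronger readings are tempting but not supported:

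- A reader might infer that the prevalence estimate itself is biased. Taking every adult gives each one the household's selection probability and does not in itself create unequal weights. Bias would need unequal household probabilities that are related to CKD, and the article shows neither.
- A reader might infer that all association tests reject too often. The rates in step 5 hold only for factors constant within a community.
- A reader might take 32 communities to mean 31 design degrees of freedom. The primary units are census sectors, and their number is not stated.

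**Conclusion.** The point holds in this form: the design is clustered at two levels, the sample size assumes a design effect of 1, the named methods assume independence in their standard form, and no provision for clustering appears. If the primary interval is computed on the same footing, it is too narrow whenever CKD is correlated within sectors or households.

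The size is not known. Under the assumed ICCs, unadjusted coverage runs from about 92% down to 72%, or from about 96% to 78% with the finite-population correction. The low end of the ICC range, where the loss is slight or absent, is credible for this population. All these figures rest on the 32 communities as a proxy for the sectors, on an average cluster size of 48, and on ICCs that the article does not supply. That uncertainty is a reason to estimate and report the design effect, not to assume that it is 1.

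**What to change.** In the Statistic analysis section:

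- Declare the sampling design in STATA, with census sector as the primary sampling unit and household as the second stage. Add weights if the actual selection probabilities differ. Take the design degrees of freedom from the actual number of sectors drawn.
- Use linearised or cluster-robust intervals for all prevalences and prevalence ratios.
- Replace the Pearson chi-square and Fisher tests with design-adjusted (Rao-Scott) tests, and use design-based comparisons for continuous variables.
- Use cluster-robust variance in the logistic and Cox models. The log-rank test has the same independence assumption, so the mortality comparison is better read from the Cox model.
- State whether inference is limited to the 139 communities and, if so, whether a finite-population correction is applied.
- Report the observed design effect, and state that the 2% sampling error at 1224 people assumes a design effect of 1.

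The cost is analysis wording. The first-stage sample is already drawn and the named program supports these methods, provided that sector and household identifiers were kept. The downside is that intervals may be wider.

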### Aims of this study

The present study (PREVRENAL) aimedto estimate the prevalence of earlystage CKD and its associated risk factors in African Brazilians from isolated quilombo communities. It also aims to evaluate demographic, clinical, and laboratory aspects of this patient population, and identify factors associated with the development of CVD.

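### Crude risk-factor associations are prevalence ratios but adjustment is by p-screened stepwise logistic regression, so crude and adjusted results sit on different scales and confounders are chosen by p-value

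*Protocol article*

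**What the plan says.** The Aims section makes CKD prevalence and "its associated risk factors in African Brazilians from isolated quilombo communities" the object of the study. The Statistic analysis section labels the risk-factor work secondary and describes it in three moves:

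- Crude step: "bivariate analysis with an unadjusted prevalence ratio estimate and a 95% confidence interval (95% CI) will be used".
- Screen: "The independent variables that present a significance lower than 0.20" go forward to the final model.
- Adjusted step: "adjustment of potentially confounding variables through the multivariate logistic regression technique performed step by step".

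The section does not mention an adjusted prevalence ratio, a conversion of the logistic results, the direction of the stepwise procedure or a retention threshold.

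The only prevalence figure is in the Study location and population section: "Total sample size was estimated per 15% CKD prevalence expectation, with 2% sampling error, and 95% confidence level", "composing a minimal sample of 1224 individuals". The same section gives 1539 individuals as finally selected.

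**The concern.** There are two separate problems, both in what the article states rather than in what it leaves out.

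The first is scale. The crude table will hold prevalence ratios and the final model will, by default, produce odds ratios. The two nearly coincide only when the outcome is rare, and an expected 15% is not rare. A reader who compares the columns to see what adjustment did will see the effect of confounding control and the effect of a new measure together. A factor with no confounding could appear strengthened by adjustment, or real confounding could be hidden.

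The second is selection. The final model is meant to control confounding, but variables enter it on a bivariate p-value and then pass through a stepwise procedure. A p-value does not identify a confounder. One that is masked in crude analysis can be lost, and intervals from the final model ignore the selection that produced it. Weak factors that survive tend to do so because their estimates happened to be large.

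The Discussion says results will go to health authorities to support public policy, so the size attached to each risk factor matters.

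**Working it through.** **The plan's own figure.** n = z² · P(1 − P) / d², with P = 0.15, d = 0.02, z = 1.96: 3.8416 × 0.1275 / 0.0004 = 1224.5. This reproduces the stated 1224 and confirms that 15% is the expected prevalence in the whole sample, not among the unexposed.

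**Scale.** Let e be the share exposed and PR the prevalence ratio.

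- Prevalence in the unexposed: p0 = P / (1 − e + e·PR)
- Prevalence in the exposed: p1 = PR · p0
- Odds ratio: OR = [p1/(1 − p1)] / [p0/(1 − p0)] = PR · (1 − p0)/(1 − p1)

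P = 0.15 is from the plan. The values of e and PR are assumptions. With e = 0.30:

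| PR | p0 | p1 | OR | Excess over PR |
|---|---|---|---|---|
| 1.5 | 0.15/1.15 = 0.1304 | 0.1957 | 1.62 | 8% |
| 2 | 0.15/1.30 = 0.1154 | 0.2308 | 2.30 | 15% |
| 3 | 0.15/1.60 = 0.0938 | 0.2812 | 3.78 | 26% |

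Sensitivity to the exposure share, from 10% to 50% exposed: PR 1.5 gives OR 1.64 to 1.61, PR 2 gives 2.38 to 2.25, and PR 3 gives 4.20 to 3.58. Sensitivity to overall prevalence, at PR 2 and 30% exposed: the excess is 4% at a prevalence of 5%, 9% at 10% and 22% at 20%. For a protective factor with PR 0.5, the OR is 0.45.

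**Selection.** The article gives no candidate list or retention rule, so these settings are assumed: 600 simulated data sets; 20 correlated binary candidates (correlation 0.2 on the underlying normal scale), each 30% exposed; three candidates each at true OR 2, 1.5 and 1.25, and 11 null; outcome prevalence about 17%. Each data set was screened at p < 0.20, reduced by backward elimination at p < 0.05, and compared with the full model without selection. Mean ORs (geometric) at n = 1539:

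| True OR | Full model | After selection, if retained | Retained in | Coverage if retained |
|---|---|---|---|---|
| 2 | 2.03 | 2.06 (+3%) | 99.8% | 95% |
| 1.5 | 1.50 | 1.62 (+8%) | 77% | 95.5% |
| 1.25 | 1.25 | 1.49 (+19%) | 35% | 91% |

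About 0.5 null factors per data set were kept, with a mean OR of 1.44 away from 1. At n = 1224 the retained means were 2.07, 1.69 and 1.56.

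**Room for a prespecified model.** 0.15 × 1539 = 231 expected cases. Even 20 terms would leave 231/20, about 11.5 cases per term.

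**The case against.** Several points on the other side are sound, and they set the limits of this one.

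- *An odds ratio is a valid measure.* This stands. A reader might infer that the adjusted odds ratios overstate the association in themselves. The documents do not support that: they do so only if read as, or set against, the prevalence ratios. The article does not say the logistic output will be read that way, and does not print the term odds ratio; it follows from the method named. The direction of an association does not depend on the scale.
- *The gap is modest for moderate effects.* This stands. A larger gap is tempting: putting 15% in the unexposed turns PR 1.5, 2 and 3 into OR 1.65, 2.43 and 4.64. With 30% exposed, though, that implies overall prevalences of 17.3%, 19.5% and 24% (0.15 × 1.15, 1.30 and 1.60), not the planned 15%. Higher prevalence in older, hypertensive or diabetic groups is plausible, but the article gives no figure for any of them.
- *Adjustment need not appear to strengthen effects.* This stands. Whether an adjusted odds ratio exceeds the crude prevalence ratio also depends on confounding, on which there are no data here. It could happen; it is not bound to.
- *The simulation settings are not the sponsor's.* This stands. The sizes are illustrative, and the inflation is negligible for strong factors.
- *A condensed article may leave the covariate list to the full plan.* True, and the absence of a list is not the complaint. The screen, the stepwise step and the two measures are stated methods.

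None of this removes the mismatch of measures or the choice of confounders by p-value.

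**Conclusion.** The point holds in this form. Followed as written, the plan sets crude prevalence ratios beside adjusted odds ratios for an outcome expected in 15%. With an assumed 30% exposed, the change of measure alone is worth 8% at PR 1.5, 15% at PR 2 and 26% at PR 3, and the crude-to-adjusted comparison could be misread by that amount. The 15% is the plan's figure; the exposure share and the prevalence ratios are assumptions, with ranges shown above.

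The p-value screen and stepwise step can lose masked confounders and, under the assumed settings, exaggerate weak factors that survive (1.25 to about 1.49, with 91% coverage), with little effect on strong ones (2.00 to 2.06).

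The change should be made, but the problem does not threaten the study: this is the secondary analysis, and the primary estimate of CKD prevalence is unaffected.

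**What to change.** 1. Report adjusted associations as prevalence ratios, the measure already used for the crude ones. Poisson regression with robust variance, a log-binomial model, or marginal standardisation of the logistic model would each do this. If odds ratios are also shown, give crude odds ratios beside them.
2. Replace the p < 0.20 screen and stepwise selection with a confounder set that the investigators fix in advance on subject-matter grounds, from variables already collected, and keep it whatever the p-values. No particular list is prescribed here. Factors that may lie on one causal path need care: adjusting them for each other changes what each coefficient means, so the set may have to differ by factor of interest.

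The cost is a change of analysis wording and of model command, with no new data. The final model will be somewhat larger and its intervals slightly wider; about 231 expected cases can carry it.
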